**Figure 3 figure3:**
[figure not shown]
Jebsen-Taylor Hand Function Test performance in a participant who has undergone transradial amputation. The participant completes standardized hand tasks using the prosthetic hand.

### FRT Description

In the FRT, the participant will stand on a flat surface, positioned sideways relative to the testing setup, with feet shoulder-width apart and stable. The test arm will be lifted laterally to shoulder height, with the fingers extended. Without moving their base of support, the participant will be instructed to reach forward as far as possible using only the upper extremity. The distance between the initial fingertip position and the furthest point reached during the movement will be measured in centimeters (cm) using a measuring tape. To enhance the reliability of the test, the measurement will typically be repeated 3 times, and the average of the 3 trials will be recorded [37]. Although FRT primarily assesses balance and reach, it provides additional information about reaching ability with the upper-limb prosthesis, which may indirectly reflect functional integration and MI performance.

### QuickDASH Questionnaire Description

The QuickDASH questionnaire will be used as a self-reported instrument designed to assess activity limitations and participation restrictions of the upper extremity [38]. The Turkish validity and reliability of the questionnaire were established by Düger et al [39]. The QuickDASH questionnaire consists of 11 items and aims to evaluate the level of difficulty individuals experience during daily living activities. Responses will be rated using a 5-point Likert scale (1=no difficulty, 2=mild difficulty, 3=moderate difficulty, 4=severe difficulty, and 5=unable to perform). Questionnaire scores will be recorded for both groups included in the study.

### JPS Description

To evaluate proprioceptive function relevant to prosthetic control, the JPS assessment will be used. JPS measures an individual’s ability to replicate a given joint angle and can be conducted using combinations of passive and active movements, under eyes-closed conditions [22].

Considering the amputation levels of the individuals who have undergone transradial amputation, all participants will undergo JPS assessment of the shoulder and elbow joints, performed bilaterally (dominant and nondominant sides where applicable) with standardized positioning while standing comfortably with feet shoulder-width apart and arms relaxed at the side before each trial. In the amputee group, assessments will be conducted with the prosthesis worn and the terminal device maintained in the closed position to ensure consistency across participants. For passive JPS, the investigator will move the limb to the target angle (eg, 30°) and then return it to the starting position, and the participant will estimate the joint angle without moving it. Participants’ vision will be occluded during assessment to prevent visual feedback, ensuring blinding to the target angle. For active JPS, the investigator first demonstrates the target angle with the participant’s eyes open. Subsequently, with eyes closed, participants actively replicate the joint angle without any physical guidance.

For the shoulder joint, angles of 90° abduction and 90° flexion will be used; and for the elbow joint, angles of 30°, 60°, and 90° flexion will be assessed. All joints will be positioned consistently at the same starting reference point for each trial to ensure measurement consistency across participants. Each angle will be measured 3 times, and the mean value will be recorded. Trials with outlier values exceeding 2 SDs from the mean or trials with measurement errors will be excluded.

All measurements will be conducted using the validated digital goniometer app DrGoniometer [40,41], which has demonstrated high validity and reliability for upper-limb joint measurements, including forearm supination and elbow flexion [40,41], although it has not been specifically validated in populations who have undergone amputation. Correctness (+5° and –5°) and reaction-time metrics are predefined. Absolute error, constant error, and variable error will be calculated to quantify accuracy and consistency. Due to the nature of the assessments, assessor blinding was not feasible; however, all measurements were conducted using a standardized protocol with fixed positioning and predefined verbal instructions to minimize bias

Covariates such as age, sex, amputation level, prosthesis experience, and tested side will be recorded and adjusted for in the statistical analyses.

All assessments will be completed within approximately 90 minutes, including short breaks as needed, in the following standardized order: MIQ-3, MCT, JTHFT, QuickDASH questionnaire, FRT, and finally JPS.

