**MI and proprioception**
Correlations between MI and proprioception measures (elbow 30°, 60°, and 90°, and shoulder 90° flexion and abduction) will be conducted.Regression models will evaluate predictors of proprioceptive performance, with covariates age, dominance, and residual limb length.

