**Missing data, outliers, and multiple comparisons**
Missing data will undergo listwise deletion.Trials with outlier values exceeding 2 SDs from the group mean will be excluded. Sensitivity analyses with and without outliers will be performed.The Bonferroni correction will be applied for multiple comparisons.

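### The joint position sense section records the mean of three readings but promises absolute and variable error, which need the individual trials; recording rule, error scores and outlier rules must be reconciled.

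*Protocol article*

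**What the plan says.** Three parts of the protocol article bear on this point.

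- **Recording rule (JPS Description):** "Each angle will be measured 3 times, and the mean value will be recorded". The section does not say whether this is the mean of the raw angles, of the signed errors or of the unsigned errors.
- **Scores to be derived (JPS Description):** "Absolute error, constant error, and variable error will be calculated to quantify accuracy and consistency".
- **Handling of single trials:** JPS Description has "Trials with outlier values exceeding 2 SDs from the mean or trials with measurement errors will be excluded". Textbox 2, under Missing data, outliers, and multiple comparisons, has "Trials with outlier values exceeding 2 SDs from the group mean will be excluded", followed by "Sensitivity analyses with and without outliers will be performed".

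Outcome Measures lists JPS error as a secondary outcome without choosing among the three scores. The planned analysis names angles but no score: "Correlations between MI and proprioception measures (elbow 30°, 60°, and 90°, and shoulder 90° flexion and abduction) will be conducted". The Results section reports that 16 of the 30 planned participants have been assessed and their data entered.

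**The concern.** Absolute error and variable error are defined on individual trials. Absolute error averages the unsigned trial errors, and variable error is the spread of the signed ones. A single mean angle carries neither: overshoots and undershoots cancel before the sign is removed, and the spread is gone. The only value that the text says is recorded therefore cannot supply two of the three scores that the text promises.

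The consistency of a participant's repositioning, which the section sets out to quantify, is what variable error measures. If it were lost, and absolute error were replaced by the size of constant error, the analyses relating imagery to proprioception would use a score that is less sensitive to trial-to-trial scatter. Timing matters too, because unrecorded readings from participants already assessed become harder to recover.

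**Working it through.** The plan gives no figure for this point, so there is none to reproduce. The check has four steps.

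**1. Definitions.** Let e_i = reading − target, for i = 1, 2, 3 (three readings, from JPS Description).

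- Constant error: CE = (e_1 + e_2 + e_3)/3
- Absolute error: AE = (|e_1| + |e_2| + |e_3|)/3
- Variable error: VE = SD of the e_i about their own mean (n − 1 divisor)

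The mean angle minus the target equals CE. The only absolute error available from it is |CE|. By the triangle inequality |CE| ≤ AE, with equality only when no two of the errors have opposite signs.

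**2. Worked triplets (degrees).**

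| Trial errors | CE | AE | \|CE\| | VE |
|---|---|---|---|---|
| −6, 0, +6 | 0 | 4.0 | 0 | 6.0 |
| −2, +3, +8 | 3.0 | 4.33 | 3.0 | 5.0 |
| +4, +5, +6 | 5.0 | 5.0 | 5.0 | 1.0 |

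The last row shows that nothing is lost from AE when the errors share a sign.

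The result depends on what is averaged. A mean of signed errors behaves like the mean angle. A mean of unsigned errors would give AE correctly but would lose the sign needed for CE. None of the three gives VE.

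**3. Expected size.** The document gives no bias or trial SD; the only angular scale is "Correctness (+5° and –5°) and reaction-time metrics are predefined". I therefore assume e_i ~ Normal(b, s) and show a range of b/s. For a normal variable with mean b and SD s,

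E|X| = s·√(2/π)·exp(−b²/(2s²)) + b·(1 − 2Φ(−b/s)).

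The numerator of the ratio uses s/√3 (mean of three trials) and the denominator uses s (single trial).

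| Bias b, in trial SDs | E\|CE\| / E(AE) | Shortfall |
|---|---|---|
| 0 | 1/√3 = 0.577 | 42% |
| 0.5 | 0.696 | 30% |
| 1 | 0.874 | 13% |
| 2 | 0.992 | 0.8% |

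Simulation with 400,000 triplets per setting agrees. In degrees, bias 0 and SD 3 gives AE 2.39 against 1.38 (42% short). Bias 3 and SD 3 gives 3.50 against 3.06 (13%). Bias 5 and SD 2 gives 5.01 against 5.00 (0.2%).

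**4. The outlier rules.** With three readings, none can lie further than (n − 1)/√n = 2/√3 = 1.15 sample SDs from their own mean. A 2-SD rule against the participant's own mean could therefore never exclude a trial. The group-mean version in Textbox 2 can, but it needs each trial value kept until group data exist. Rerunning an analysis with and without excluded trials needs those values as well.

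**The case against.** The strongest objection is that the document never says that only the mean is kept. A reader might infer that trial readings are thrown away, so that variable error is definitely out of reach and proprioceptive error is definitely understated. The text does not support that. The promise of variable error, the exclusion of single trials, the group-mean reference and the sensitivity analyses all presuppose trial values. The mean may simply be the summary score per angle. A condensed article may also leave database fields to the full protocol.

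This objection stands as far as it goes: the loss is conditional. It does not remove the conflict. The mean is the only value stated to be recorded, and the FRT Description uses the same construction where the average plainly is the datum. An assessor following the sentence would enter one number per angle. No sentence says that the errors are calculated per trial. That other rules need trial values does not show that the values are stored.

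A second tempting inference is that an inconsistent but unbiased participant would appear to have perfect position sense. A particular triplet can average to zero, but in expectation 58% of absolute error remains at zero bias (0.577 above). A bias of known size or direction in the group comparison has not been shown either.

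**Conclusion.** The concern holds as an internal conflict with a conditional consequence. The recording sentence, the promised error scores and the trial-level rules do not fit together as written.

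If the recording sentence is followed literally and the value is the mean angle, variable error is lost whatever the bias. Absolute error reduces to |constant error|, with an expected shortfall from about 42% at zero bias to under 1% at a bias of 2 trial SDs, and none for a participant whose three errors share a sign. These percentages assume independent normal trial errors with a common SD, and the document does not show where in the range this study lies. The 42% is the upper end and should not be read as the expected effect.

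Constant error is unaffected on that reading. JPS is a secondary outcome, so the MIQ-3 primary comparison is untouched. The point gives no ground for making absolute error the sole analysed JPS score; which score enters the tests is a separate choice.

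**What to change.** Reconcile JPS Description with the outlier paragraph of Textbox 2 by replacing the recording sentence with:

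*All three readings per angle, side and mode are recorded; absolute error is the mean of the unsigned trial errors, constant error the mean and variable error the SD of the signed trial errors.*

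In the same edit, state the same reference mean for the 2-SD exclusion in both places, since the own-mean version cannot operate with three readings.

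For the 16 participants already assessed, recover the trial readings from source forms or the goniometer app. Where they cannot be recovered, report how many participants contribute to each error score and state that absolute and variable error are analysed in a reduced sample.

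**Cost.** Two further data fields for each mean now entered, for the 30 − 16 = 14 participants still to be assessed, plus back-entry for the 16. If trial readings are already stored, the cost is one sentence. The real downside arises if none of the 16 can be recovered: under the planned listwise deletion, absolute and variable error would be available for only about 14 of 30 participants, while constant error would remain available for all with a recorded mean angle.

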**Figure 1 figure1:**
[figure not shown]
Study flowchart.

The study timeline and procedures are summarized as follows: ethics approval was obtained from the institutional ethics committee on May 9, 2024, and funding was received from the Scientific and Technological Research Council of Turkey (TÜBİTAK) on April 25, 2025. Participant recruitment and data collection started on April 25, 2025, with 15 participants planned per group. Assessments and interventions include tests of MI ability, upper limb functional tests, and proprioception test. Follow-up will include ongoing monitoring and assessment of all participants. Data analysis will be completed after all data are collected. The study is expected to be completed in June 2026.

The sampling frame consists of all eligible individuals with unilateral transradial amputation who meet the inclusion criteria across the collaborating clinics during the recruitment period. Participants will be recruited consecutively, applying identical inclusion and exclusion criteria across centers.

Although participants will be recruited from different clinics, all assessments will be performed by a single trained researcher (the first author) using the same equipment and standardized procedures at the prosthetics and orthotics research and application center. This approach ensures measurement consistency and minimizes the risk of selection bias.

This study was reported in accordance with the STROBE (Strengthening the Reporting of Observational Studies in Epidemiology) statement for cross-sectional studies (Multimedia Appendix 1). The related TÜBİTAK 1002-A project report is provided in Multimedia Appendix 2.

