### Outcome Measures

According to the study hypothesis, the primary outcome is MIA assessed using the MIQ-3, which was selected as the primary end point given its central role in prosthetic motor control, motor learning, and functional adaptation in individuals who have undergone transradial amputation.

The secondary outcomes include the following:

Upper-limb functional performance, assessed using the Box and Block Test (BBT), Jebsen-Taylor Hand Function Test (JTHFT), and the Disabilities of the Arm, Shoulder, and Hand (QuickDASH) questionnaireMI performance indicators, including the Mental Chronometry Test (MCT) and hand mental rotation task, as secondary measures of MIAProprioceptive and sensorimotor accuracy, measured by joint position sense (JPS) error using a validated digital goniometer app (DrGoniometer [CDM SrL])General balance and flexibility, evaluated by the Functional Reach Test (FRT) as an indicator of overall functional stabilityCognitive and psychological screening, including the Standardized Mini-Mental State Examination (SMMSE), Beck Depression Inventory (BDI), and Visual Analog Scale (VAS) for pain intensity

Each participant will be assessed once, as this is a cross-sectional study with no intervention. To minimize potential bias, all assessments will be performed by trained evaluators following standardized protocols. Participants will be recruited according to predefined eligibility criteria to reduce selection bias, and data will be systematically recorded to prevent information bias. As no intervention is applied, performance bias is not applicable.

To minimize the risk of type I error resulting from multiple comparisons, the Bonferroni correction will be applied to secondary outcome analyses.

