### MIQ-3 Description

The MIQ-3, originally developed by Williams et al [31], will be used to assess imagery ability in all individuals included in the amputee and control groups. The Turkish validity and reliability study of this questionnaire was conducted by Dilek et al [32]. The MIQ-3 consists of 12 items and evaluates internal visual imagery, external visual imagery, and kinesthetic imagery abilities through 4 actions for each domain. These actions include leg raising, jumping, shoulder flexion, and forward bending. The movements are designed to assess MI capacity in internal, external, and kinesthetic dimensions.

Participants will initially perform each movement physically. They will then be asked to mentally perform the same movements as a cognitive task. This mental imagery task will be rated using a 7-point Likert-type scale (1=very hard to see or feel and 7=very easy to see or feel). For scoring, the average score of the 4 movements corresponding to each subdimension will be calculated.

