### MCT Description

MCT is an objective method used to evaluate the temporal accuracy of MI [33]. In this study, the MCT will be administered using the BBT. Participants will first be asked to physically transfer 15 blocks from one compartment to another, and the time taken will be recorded. Subsequently, the same task will be mentally imagined after removing the test apparatus from view. The duration for the imagined transfer of each block will be verbally indicated by the participant and recorded accordingly.

The difference between the actual and imagined durations will be used to calculate the mental chronometry ratio, using the following formula:

mental chronometry ratio = |actual time − mental time| / actual time

A ratio closer to 0 indicates that the imagined movement duration closely approximates the actual movement, reflecting a higher level of MIA.

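### Assessor blinding is ruled out altogether, although only blinding to group is impossible; blinding to imagery scores is largely feasible and would protect the secondary association analyses

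*Protocol article*

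**What the plan says.** On who assesses, the Study Design section (text after Figure 1) says that "all assessments will be performed by a single trained researcher (the first author) using the same equipment and standardized procedures". The Outcome Measures section says instead that "all assessments will be performed by trained evaluators following standardized protocols", in the plural.

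On blinding, JPS Description says "Due to the nature of the assessments, assessor blinding was not feasible" and does not say to what the assessor cannot be blinded. The safeguard it offers is that "all measurements were conducted using a standardized protocol with fixed positioning and predefined verbal instructions to minimize bias". The same section sets the session "in the following standardized order: MIQ-3, MCT, JTHFT, QuickDASH questionnaire, FRT, and finally JPS".

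On how imagery is recorded, the MIQ-3 Description says "This mental imagery task will be rated using a 7-point Likert-type scale", without saying who fills in the form or when it is scored. The MCT Description says "The duration for the imagined transfer of each block will be verbally indicated by the participant and recorded accordingly".

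On discarding data, JPS Description says "Trials with outlier values exceeding 2 SDs from the mean or trials with measurement errors will be excluded". Measurement error is not defined.

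Textbox 2 of the Statistical Analysis section then correlates imagery with the functional tests and the joint position measures. It also plans regressions for both, with imagery as the predictor of function.

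**The concern.** The study has two aims: to compare imagery ability between groups, and to relate imagery ability to function and proprioception. They call for different blinds. For the group comparison the relevant blind is to group, and a worn prosthesis makes that impossible. For the associations the exposure is the imagery score, so the relevant blind is to that score. The article treats the two as one and gives up both.

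An assessor who has just seen how well someone imagines movement can be influenced, without intending it, when timing tasks, giving encouragement, reading a tape, positioning a limb or deciding that a trial went wrong. Any such influence tracks the imagery score, so it goes straight into the correlations and regression slopes. It cannot be separated from a true association afterwards. A fixed script limits what is said to the participant; it does not govern which trials are thrown out.

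**Working it through.** The plan states no figure on this point, so there is none to reproduce. The check is mainly a reading of the sections together.

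1. **Is the assessor exposed to imagery results?** For chronometry, yes: the times are spoken and recorded in the session, and on the single-researcher account the same person goes on to the other tests. For the MIQ-3 it is not stated; nothing in the plan prevents it.
2. **Which later measures are exposed?** The listed order puts JTHFT, FRT and joint position sense after both imagery tests. JTHFT is scored from task times (no timing device is named), FRT is read from a tape, and in joint position testing the investigator moves the limb or shows the target angle. QuickDASH is self-reported and so less exposed. The Box and Block Test and the Orientate app do not appear in the order, so the sequence argument is not documented for them.
3. **Which exclusions are discretionary?** The 2-SD rule is numeric, and Textbox 2 asks for a sensitivity analysis of outliers. The measurement-error clause has no definition and is not clearly covered by that sensitivity analysis.
4. **Does the reason for not blinding reach imagery scores?** The prosthesis reveals group. Nothing in the article explains why the assessor must know MIQ-3 totals, the chronometry ratio or Orientate results during the session.

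**Illustration of size, under an assumption.** Let x be the standardised imagery score, with no true association, and let knowledge of it shift the outcome by b, so that y = b·x + e, where x and e are independent with SD 1. The induced correlation is r = b/√(1 + b²). For b = 0.2, r = 0.2/√1.04 = 0.196. Simulating the Pearson test (40,000 runs, two-sided 5%, no multiplicity correction) gives the following chance of a significant result per test:

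| b (assumed) | induced r | n = 15 | n = 30 |
|---|---|---|---|
| 0 (blind) | 0 | 5.1% | 5.2% |
| 0.1 | 0.10 | 6.5% | 8.1% |
| 0.2 | 0.20 | 11.1% | 18.4% |
| 0.3 | 0.29 | 18.0% | 34.0% |
| 0.5 | 0.45 | 40.1% | 72.1% |

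Here n = 15 is the amputee group alone and n = 30 is both groups pooled; the article does not say which will be used. The documents support no value of b.

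**The case against.** Much can be said for the plan. It does not say that the assessor sees MIQ-3 ratings: participants may already fill in the form themselves, and a condensed article need not describe form handling. Subscale means and the chronometry ratio have to be calculated, so the assessor may never hold a score in mind. Hand timing of the JTHFT is not stated either. If the plural in Outcome Measures is correct, the single-assessor premise weakens. The later measures are fairly objective: task times, distances averaged over three trials, and angles from a goniometer app. Bonferroni correction would lower the false-positive rates above, and the planned regressions adjust for covariates. Finally, chronometry times are spoken aloud, so with one assessor the claim of infeasibility is partly right for imagery too.

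These points stand as limits. A reader might infer that the assessor certainly knows all imagery scores; the documents show this only for the chronometry times. A reader might also infer that the main result is compromised. It is not, because the primary MIQ-3 group comparison does not depend on this blind.

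What the objection leaves standing is the blanket statement itself. It is an explicit position, not an omitted detail, and it is wider than its reason. Bonferroni correction and covariate adjustment do not remove a bias that moves with the imagery score.

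**Conclusion.** The point holds as a cheap improvement to secondary analyses that serve a stated objective. The article should distinguish blinding to group, which is impossible, from blinding to imagery scores, which is largely feasible. As written, the plan does not prevent the assessor from knowing imagery results while measuring JTHFT, FRT and joint position sense and while discarding joint position trials.

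The size of any bias cannot be derived from the documents. The tabulated rates rest on an assumed slope, an unadjusted correlation and an uncorrected 5% test; they should not be read as the study's error rate. The conclusion also rests on the single-researcher statement, which must be reconciled with the plural in Outcome Measures.

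**What to change.** - In JPS Description, limit the statement on feasibility to group status, and say that the assessor is kept blind to imagery scores as far as possible.
- Make Study Design and Outcome Measures agree on the number of assessors. If there is more than one, imagery testing and outcome testing can simply be split between them.
- For the participants still to be assessed (30 − 16 = 14 at the November 2025 count), have the participant complete the MIQ-3 form and confirm that all 12 items are answered. Check it for blanks only, seal it, and score it after joint position testing. The blank check matters because Textbox 2 deletes incomplete cases listwise, and a missed item could cost one of 15 participants in a group on the primary outcome.
- Calculate the chronometry ratio and export the Orientate results only after the session.
- For all 30 participants, decide measurement-error exclusions on a coded file without group or imagery scores, and report results both including and excluding those trials. This needs the individual trial values; the planned variable error needs them too.

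The cost is an envelope, a coded file and some rewording, with no extra staff. The downsides should be stated in the report. Spoken chronometry times stay visible, so blinding is partial. A missed MIQ-3 item may be noticed later than now. For the 16 already assessed only the exclusion step can be blinded, which belongs among the limitations. Data cleaning had begun but no analysis had been run at the time of the article, so the coded file is best set up before cleaning goes further.
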